To address the challenges outlined, we developed a proof-of-concept intervention platform to deliver in situ support for child ER during everyday emotionally charged situations, such as the child feeling angry, anxious, or sad. On the basis of a 2-year-long development [31,32], we worked with children, parents, and prevention science experts to co-design an intervention that would support children in strengthening their ER skills. The research prototype was then produced by the Committee for Children (a US-based nonprofit developer of socioemotional learning programs) and Sproutel [33], resulting in a commercial-grade therapeutic toy called Purrble [34].

The initial research prototypes were designed as the first instantiation of a novel *situated* intervention model, which is delivered through an interactive, socially assistive robot sent home with the child or used in schools, without any previous training for either the child or their parent or caregiver. As such, the psychological effects of Purrble are assumed to arise from repeated *bottom-up* support in situ, instead of relying on the traditional *top-down* training contexts delivered through workshops or therapy sessions. In particular, the intervention logic model relies on a 3-stage approach: (1) enabling the child to downregulate emotional moments in situ can (2) provide a preferred alternative to maladaptive emotion regulatory strategies (eg, rumination or suppression) and, over time, (3) lead to shifts in child ER competence [31]. For a detailed description of the hypothesized mechanisms and their links to the intervention design choices, see the *Intervention* section.

To date, 2 qualitative deployment studies have investigated the engagement and acceptability of the prototype in young children’s homes, as well as subjective indicators of effects on emotion regulatory practices (whether positive or negative), as reported by parents and children [31,32]. Findings from these studies have been very positive: all 25 children engaged with the prototype throughout the deployments, all wanted to keep it for longer, and all described how they naturally incorporated it into their everyday routines and gravitated toward it when they needed to downregulate their emotions, including anger, anxiety, or just needing to relax.

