Deployments with the research prototypes underpinning the current Purrble [31,32] show that, across all 25 families, children reported that the smart toy was incorporated into the children’s ER practices and engaged with naturally in moments the children wanted to relax or calm down. Specifically, the data from [31] shows that the children interacted with the toy throughout the week-long deployment (eg, average active use for 74.9, SD 64.1 minutes per day; median 60.5), they found the experience enjoyable, and all children requested to keep the toy longer. Children’s emotional connection to the toy appears to have driven this strong engagement. Parents reported satisfaction with and acceptability of the toy. No quantitative data on changes in ER were collected in previous studies because of the small sample size and the focus on feasibility and understanding of appropriation within families.

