#### Secondary Outcome Measures

##### Daily Parent Report EMA

In addition to the primary EMA outcome, we will collect several other daily EMA parent reports. The psychological constructs targeted are the *child’*s *general mood* and *daily engagement with the toy.*

The *child’s daily mood* is measured by selected Modified Differential Emotions Scale (mDES) [68] emotion triplets, balancing 2 negative and 2 positive sets, while being informed by previous qualitative studies. The items are listed as follows, all measured on a visual analog scale [62,63], with *not at all* and *extremely* as the anchors:

How stressed, nervous, or oevrwhelmed did your child feel today?How joyful, glad, or happy did your child feel today?How angry, irritated, or annoyed did your child feel today?How proud, confident, or self-assured did your child feel today?

The *daily engagement item* asks about the general perception of engagement with the toy (*How much did your child play with the toy today?*)*,* measured on a visual analog scale [62,63], with *not even once* and *they were inseparable* as the anchors.

Finally, we will include a *series of explorative items that examine the child’s reaction after potentially triggering events*. We will first ask the parents *Did anything happen today that would typically upset your child?* If yes, the protocol follows with several questions collecting qualitative and quantitative information regarding the number of such situations, the intensity and length of subsequent children’s negative reactions, how many of these situations the child used the toy, who initiated the use, how helpful or unhelpful it was, and an opportunity to share open-ended comments or observations. The purpose of these items is to gain a qualitative understanding of the toys’ use in challenging situations and to guide post deployment interviews.

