##### Secondary Hypotheses

Intervention effects will be moderated by daily engagement with toy and weekly data from the TWEETS questionnaire. In addition, we expect to see between-group differences in favor of Purrble for the secondary daily EMA parental-report outcomes: *an increase* in the *positive mDES items* and a *decrease* in the *negative mDES items*.

Finally, as exploratory analyses, we will investigate the following hypotheses for weekly outcome measures:

The decrease in *parent-reported emotional and behavioral difficulties* (as measured by the SDQ) will be greater in the intervention group (smart toy) than in the active control group (noninteractive toy).*The decrease in ER lability* and *increase in emotion regulation competence* (as measured by the Lability or Negativity subscale and Emotion Regulation subscale questionnaires respectively) will be greater in the intervention group than in the active control group (noninteractive toy).*Behavioral, cognitive, and affective engagement* with the intervention, as measured by the adapted *TWEETS questionnaire for parents*, will be higher for the intervention than the control group.The decrease in *child-reported emotion dysregulation* (as measured by the DERS) will be greater in the intervention group than in the active control group (noninteractive toy).The decrease in *child-reported entity beliefs of emotion regulation* (as measured by the ER mindset questionnaire) will be greater in the intervention group than in the active control group (noninteractive toy).

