#### Data Analyses

All analyses of daily EMA outcomes (the primary outcome of daily ER and secondary outcomes of engagement with the toy and mood), as well as the analyses of the weekly outcomes, will be conducted using random-effect models for longitudinal regression. These models consider the nested nature of repeated-measures data and are robust to data missingness and violations of the normality assumption. The regression models will examine the difference in the outcome as a function of the assigned condition (Purrble vs active control). The models will adjust for the baseline levels of the score on the total difficulty scale in the SDQ to decrease noise. To account for participant-to-participant variability in EMA scoring as well as in trajectories of change in EMA scores over time, we will include a random intercept and random slope for time. All analyses will be conducted on an intent-to-treat basis and will use data from all randomized participants regardless of their level of participation.

A separate model will be fitted to each outcome. Given that this is an exploratory trial, we will not formally adjust for multiple comparisons. However, we will be cautious in our conclusions about any significant findings and will interpret all results in light of all performed analyses.

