To examine the link between engagement with the intervention and ER outcomes, we will conduct 3 types of exploratory analyses: first, given that we hypothesize that Purrble will be more engaging than the control-condition stuffed animal, we will examine whether intervention engagement is influenced by the treatment condition. To do so, we will regress our daily measure of engagement on the treatment condition, controlling for the previous day’s engagement to reduce noise. Similarly, we will regress the weekly TWEETS scores on the treatment condition, controlling for the previous week’s engagement. Second, we will examine whether engagement moderates the intervention impact on both our primary outcome, the daily measure of emotional regulation, and the weekly ERC and SDQ measurements. For the daily model, we will use our primary measure, the EMA assessment of ER, as the dependent variable, and will include, as regressors, treatment indicators and the EMA measure of engagement, as well as a term for their interaction. To decrease noise, the model will also include as a covariate the previous day’s score on the ER measure. Similarly, for weekly models, we will regress the weekly ERC and SDQ scores on terms for the treatment indicator, TWEETS score, and their interaction. As in the daily model, we will also include a term for the ERC or SDQ score of the previous week to reduce noise. As an alternative approach, we will consider using the weekly average of the daily EMA engagement scores rather than TWEETS for the weekly analyses of the moderating influence of engagement, as these 2 scales tap into different aspects of the engagement experience.

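### The daily moderation model's single engagement term measures almost only day-to-day variation within families, so it says little about whether more-engaged families benefit more

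*Protocol article*

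**What the plan says.** Under Secondary Hypotheses the protocol states: "Intervention effects will be moderated by daily engagement with toy and weekly data from the TWEETS questionnaire". It gives neither the level (between families, or between days within a family) nor a direction.

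Data Analyses then fixes the daily model. The outcome is the daily emotion regulation (ER) score, and the model "will include, as regressors, treatment indicators and the EMA measure of engagement, as well as a term for their interaction". In addition, "the model will also include as a covariate the previous day’s score on the ER measure". All daily and weekly outcome analyses "will be conducted using random-effect models for longitudinal regression", and for the daily scores "we will include a random intercept and random slope for time". No family-mean engagement term is named. The weekly models have the same form, with the TWEETS score as the engagement term. A weekly average of the daily engagement item is offered as an alternative for those weekly models only, and it is not a split into two levels either.

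Daily engagement is one parent-rated item: "How much did your child play with the toy today".

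**The concern.** Daily engagement varies in two ways. Some children use the toy more than others over the whole month, and a given child uses it more on some days than on others. A treatment effect could depend on either. With one engagement term and one interaction, the model assumes the two dependences are equal and estimates a weighted blend. In a random-intercept model with many days per family and a strongly person-specific outcome, nearly all the weight falls on the within-family part.

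The logic model's level 3 is a cumulative claim: repeated soothing over weeks shifts the child's ER practice. That is mainly about how much a family uses the toy overall, which the planned coefficient hardly measures.

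The protocol also gives a reason why the two effects may differ. The Introduction says that children in the pilot work "gravitated toward it when they needed to downregulate their emotions", and the Intervention section says the toy was "engaged with naturally in moments the children wanted to relax or calm down". If a hard day both lowers the ER score and raises toy use, the day-level association could be negative while the family-level one is positive. A null or negative interaction could then be read as evidence against the logic model when it speaks only to day-level use.

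**Working it through.** **Plan's own figure.** The protocol gives no figure for the moderation analysis, so there is none to reproduce.

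**Inputs from the protocol.** T = 28 days (daily over 4 weeks). Correlation between repeated measures 0.75 (Sample Size and Power), taken as outcome variance split into a family part s2u = 0.75 and a day part s2e = 0.25. Simulations used the 120 families of that section.

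**Assumed input.** p, the share of engagement variance lying between families (engagement ICC). The protocol does not give it; range 0.3 to 0.9, taken as equal in both arms.

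**Weights in a random-intercept model.**
- within = (T − 1)(1 − p) / s2e
- between = (p + (1 − p)/T) / (s2u + s2e/T)
- between-family share = between / (between + within)

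For p = 0.5: within = 27 × 0.5 / 0.25 = 54; between = 0.518 / 0.759 = 0.68; share = 0.68 / 54.68 = 1.2%.

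| p | within | between | share, daily model |
|---|---|---|---|
| 0.3 | 75.6 | 0.43 | 0.6% |
| 0.5 | 54.0 | 0.68 | 1.2% |
| 0.7 | 32.4 | 0.94 | 2.8% |
| 0.9 | 10.8 | 1.19 | 9.9% |

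Over the same range of p, the share is 1.6 to 24% if the correlation is 0.5, and 3.6 to 42% if it is 0.3.

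**Weekly models.** Same formula with T = 4, outcome ICC 0.75 (assumed for the weekly scales) and a random intercept, so s2u + s2e/T = 0.8125.
- p = 0.5: within = 3 × 0.5 / 0.25 = 6; between = 0.625 / 0.8125 = 0.77; share 11%.
- p = 0.7: 0.95 / (0.95 + 3.6) = 21%.
- p = 0.9: 1.14 / (1.14 + 1.2) = 49%.

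**Simulation check.** The closed form omits the random time slope and the lagged score, so the planned model was also simulated with both, plus baseline SDQ (60 trials per scenario, correlation 0.75, p = 0.5). The moderation sizes are assumptions.

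| True between | True within | Planned interaction | Split model: between, within |
|---|---|---|---|
| +0.30 | −0.10 | −0.096, significantly negative in all 60 | 0.275, −0.101 |
| +0.30 | 0 | 0.003, never significantly positive | 0.279, −0.001 |
| +0.30 | +0.30 | 0.299 | 0.291, 0.299 |

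The first row agrees with the closed form: 0.0125 × 0.30 − 0.9875 × 0.10 = −0.095. Dropping the lagged score left the planned interaction in these scenarios unchanged to three decimals.

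**Power of the family-mean interaction.** In these three scenarios, the split model without the lagged score detected the true 0.30 in 25 to 28% of trials. In other assumed scenarios (lower outcome correlation, higher p, or both) the figure was 40 to 50%.

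**A side effect of the lagged score.** With a day-to-day carry-over of 0.4 in the outcome, the family-mean interaction in the split model was 0.167 with the lagged score and 0.279 without it, because part of a lasting effect is absorbed by the previous day's score.

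**The case against.** The strongest reply is that the hypothesis speaks of daily engagement, that the primary outcome is described as a repeated within-subject measure, and that level 1 of the logic model concerns in-the-moment soothing. On that reading a mostly within-family coefficient is the one wanted, and the planned term answers the question. This stands. It narrows the point to two things: the protocol does not say which level it means, and the planned term does not serve the level 3 claim.

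A reader might infer that the planned model reports the wrong sign. The documents do not support that. In the scenario with a negative result, the model correctly recovers a negative within-family moderation that was built in; it simply differs from the between-family one. The evidence that the two diverge is qualitative and indirect. The engagement item asks about play in general, toy use in upsetting situations is collected by separate items, and the pilot accounts also mention relaxing and everyday routines.

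A reader might also infer that lack of centring is the defect. The article is silent on centring, and subtracting the overall mean would leave the interaction unchanged.

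Finally, the analysis is labelled exploratory, the authors promise cautious conclusions, and the primary analysis is unaffected. That limits the consequence but does not make the coefficient interpretable. The mediation analysis uses each family's average TWEETS score but has no interaction term, so it does not fill the gap.

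**Conclusion.** The point holds for the daily moderation model as the protocol specifies it. At the protocol's correlation of 0.75 and 28 days, between-family information makes up about 1 to 3% of the engagement coefficient for an assumed engagement ICC of 0.5 to 0.7, and about 10% at 0.9. The planned interaction is close to a pure day-level quantity. The conclusion weakens if the true correlation is much lower and engagement is almost entirely a family trait.

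Divergence between the two effects is a possibility the protocol makes plausible, not a demonstrated error; if they are equal, the planned model is adequate. It would be too strong to say the weekly models are affected to the same degree: their between-family share is about 11 to 49% under the assumed ICCs, so they yield a real mixture that is hard to assign to either level. This is a worthwhile, inexpensive correction to a secondary exploratory analysis.

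**What to change.** In the daily model, replace the single engagement term with two: the family's own mean engagement over the deployment, and the daily deviation from that mean. Give each its own interaction with condition. Do the same in the weekly models, for TWEETS and for the weekly average of the daily item.

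State in advance that the family-mean interaction addresses whether more-engaged families benefit more, and that the deviation interaction addresses whether the effect is larger on days (or weeks) of more use, with an expected direction for each. If the previous day's score stays in the model, also report the family-mean interaction without it, because the lag can shrink that coefficient.

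Cost: one derived variable and a few sentences, with no new data and no change to the primary analysis. There will be two interaction coefficients instead of one. The family-mean interaction will be imprecise (about 25 to 30% power for a moderation of 0.3 per SD at an engagement ICC of 0.5, both assumed). It also remains observational, because engagement is measured after randomisation. Report it with a confidence interval, labelled exploratory, and do not read a non-significant result as absence of moderation.

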### Participant Eligibility Criteria

Given Purrble’s intended use as a targeted prevention intervention, we will recruit an *enriched* population of neurotypical children, aged 8-10 years, from families in the United States. The enrichment consists of recruiting families where the child is seen as struggling with some level of ER difficulty (as reported by their parent) but is not undergoing clinical treatment.

The specific inclusion criteria were a child aged 8-10 years, parent-reported score of ≥10 for the total difficulties score on the Strength and Difficulties Questionnaire (SDQ). The exclusion criteria for the child were current participation in another mental health intervention. In addition, an exclusion criterion for the parent and/or the child is not being fluent in English (as all measurement scales are in English).

The target child age range has been selected as collecting self-report measures from young children is a well-known challenge, especially when inquiring about complex cognitive concepts such as those involved in ER [60,61], and our pilot work in families and schools suggests that acceptability for the toy is high with children of this age, with children aged 8-10 years still using the toy as intended.

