Finally, as our logic model postulates that engagement may also mediate the impact of intervention, we will also conduct an analysis of the mediating role of engagement. Given the ambiguities of mediation analyses in longitudinal settings and the lack of consensus on best practices, for this analysis, we will follow the original Baron and Kenny approach to establishing mediation [75]. To do so, we will use, as our outcome variables, the change scores for the emotion-regulation measures (ERC and SDQ) from baseline to the end of study (end of week 4). To measure engagement, we will use the average of the weekly TWEETS assessments over the course of the study. To examine the mediating role of engagement, we will conduct 3 sets of analyses: first, we will estimate the impact of the treatment condition on the change in ER by regressing the emotion-regulation change score on the indicator of the treatment condition. Second, to examine whether treatment had an impact on engagement, we will regress the average of the weekly TWEETS assessments on the indicator for the treatment condition. Finally, we will estimate a model that regresses the ER change score on both the treatment indicator and engagement. To assess preliminary evidence on the mediating role of engagement, we will examine the magnitudes of effect coefficients in all models, as well as statistical significance, to determine whether the inclusion of engagement in the model has reduced the impact of the treatment condition. Given that the ERC and SDQ tap into different aspects of emotion regulation, we will conduct these analyses for both ERC and SDQ change scores.

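### The mediation regressions use ERC and SDQ change scores without the matching baseline: a modest loss of precision for the total effect, and an untested assumption for the engagement coefficient

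*Protocol article*

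**What the plan says.** The mediation paragraph of Data Analyses sets out three regressions. The outcomes are "the change scores for the emotion-regulation measures (ERC and SDQ) from baseline to the end of study (end of week 4").

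- **Total effect:** estimated by "regressing the emotion-regulation change score on the indicator of the treatment condition".
- **Engagement:** "we will regress the average of the weekly TWEETS assessments on the indicator for the treatment condition".
- **Joint model:** "Finally, we will estimate a model that regresses the ER change score on both the treatment indicator and engagement".

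Coefficient sizes and significance are then compared "to determine whether the inclusion of engagement in the model has reduced the impact of the treatment condition". No baseline ERC or SDQ appears among the regressors.

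Two other statements in the same section bear on this. For the random-effect longitudinal models: "The models will adjust for the baseline levels of the score on the total difficulty scale in the SDQ to decrease noise". For the weekly moderation models: "we will also include a term for the ERC or SDQ score of the previous week to reduce noise".

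Table 1 shows both SDQ and ERC collected at baseline. Under Participant Eligibility Criteria, entry requires a "parent-reported score of ≥10 for the total difficulties score on the Strength and Difficulties Questionnaire (SDQ").

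**The concern.** A change score contains its own baseline with a negative sign, so part of its variance is predictable from a quantity already in hand. Leaving that quantity out has two separate consequences.

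First, the total-effect regression compares randomised arms. It stays unbiased but carries more residual variance than it needs to.

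Second, engagement is not randomised. In the joint model its coefficient, and so the shift in the treatment coefficient on which mediation is judged, depends on how engagement relates to the child's starting level. A raw change score and a baseline-adjusted model make different assumptions about that relation and can give different answers. The plan commits to one form without a check. It also departs from its own moderation models, which carry the prior score.

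**Working it through.** The article gives no figure for the mediation analysis, so there is none to reproduce.

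**Inputs.** From Sample Size and Power: d = 0.3, alpha .05 (taken as two-sided), 120 families and 20% dropout, so 120 × 0.8 = 96 analysed. The correlation of 0.75 is stated there for the daily measure. Its use for ERC or SDQ, and the alternative of 0.5, are assumptions. The variance ratios below do not depend on the sample size.

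**Precision, unselected sample, unit score variance.** Let rho be the baseline-to-week-4 correlation. The variance of the raw change is 2(1 − rho); after baseline adjustment it is 1 − rho². The ratio of adjusted to raw is (1 + rho)/2. Power treats d = 0.3 as a difference on the raw-score SD.

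| rho | Raw | Adjusted | Ratio | Saving | Power, raw | Power, adjusted |
|---|---|---|---|---|---|---|
| 0.75 | 0.500 | 0.4375 | 0.875 | 12.5% | 53.9% | 59.5% |
| 0.5 | 1.000 | 0.750 | 0.750 | 25% | 30.7% | 39.0% |

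Equivalently, the standard error without baseline is larger by √(2/(1 + rho)) − 1, that is 7% and 15%.

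**Effect of the SDQ entry rule.** Assume normal scores and, for illustration, a cut 0.5 SD above the mean. The baseline variance among entrants falls to 0.268. The slope of change on baseline stays at −(1 − rho) and the residual variance stays at 1 − rho². The variance of the SDQ change is then (1 − rho)² × 0.268 + (1 − rho²).

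- rho 0.75: 0.0168 + 0.4375 = 0.454. Saving 0.0168/0.454 = 3.7%; correlation of change with baseline −√0.037 = −0.19, against −0.35 unselected.
- rho 0.5: 0.067 + 0.750 = 0.817. Saving 0.067/0.817 = 8.2%; correlation −√0.082 = −0.29, against −0.50 unselected.

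ERC is selected on only indirectly, so its figures should shrink less.

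**Engagement coefficient.** Suppose there is no true effect of toy or engagement, and engagement correlates at r with the observed baseline. Without baseline in the joint model, the expected standardised engagement coefficient is −(1 − rho)r: −0.15 at rho 0.5 and −0.075 at rho 0.75, for r = 0.3. The table gives simulated rejection rates for that coefficient (2,000 runs, N = 120, assumed correlation 0.3, engagement 0.5 SD higher in one arm). The nominal rate is about 5%.

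| Engagement follows | Entry | rho | Raw change | Baseline added |
|---|---|---|---|---|
| Observed baseline | unselected | 0.5 | 37% | 5% |
| Observed baseline | unselected | 0.75 | 20% | 4% |
| Observed baseline | above cut | 0.5 | 7% | 5% |
| Observed baseline | above cut | 0.75 | 6% | 6% |
| Stable severity | unselected | 0.5 | 5% | 27% |
| Stable severity | unselected | 0.75 | 5% | 19% |
| Stable severity | above cut | 0.5 | 16% | 26% |
| Stable severity | above cut | 0.75 | 12% | 20% |

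With correlation 0, both forms stay at about 5%. Neither form is protected in every row.

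**The case against.** **The baseline SDQ sentence may already cover this.** That sentence follows the description of the random-effect models; a single change score per child is a different model. On the broadest reading it would supply baseline SDQ total and never baseline ERC. Nor is this detail left to another document, since the mediation regressors are written out.

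**A reader might infer that selection at SDQ 10 or more makes matters worse.** The reverse holds. Selection lowers the average score at week 4, but that fall is common to both arms and goes into the intercept. Narrowing the baseline range weakens the correlation of change with baseline and shrinks both the precision gain and, where engagement follows the observed score, the spurious association.

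**A reader might also infer that regression to the mean will pass as mediation at the rates in the upper rows of the simulation table.** The documents do not support that. They give no correlation between engagement and severity. The rates are for the engagement coefficient alone, whereas the plan first estimates the treatment effect and then asks whether it shrinks. With no true toy effect, the first step is significant in only about 5% of trials. The expected shift in the treatment coefficient is also small: with a 0.5 SD arm difference in engagement it runs from 0.5 × 0.05 = 0.025 SD (rho 0.75, r 0.2) to 0.5 × 0.15 = 0.075 SD (rho 0.5, r 0.3).

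**Adjustment is not a clean cure.** This objection stands. If engagement follows the child's stable severity, adding baseline makes the engagement coefficient worse.

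**The stakes are low.** This stands too. The article calls these analyses exploratory, seeks only preliminary evidence from them, and leaves the primary outcome untouched.

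**Conclusion.** The point holds in a limited form. The change-score regressions omit a baseline that is collected, which wastes some precision in the randomised total-effect comparison: 12.5% of the variance at rho 0.75 and 25% at rho 0.5 in an unselected sample, and about 4-8% for SDQ under the assumed cut. The total effect is not biased.

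For the engagement coefficient, the documents do not show that either form is right. The raw change score is vulnerable if engagement depends on the observed baseline, and the adjusted model is vulnerable if it follows stable severity. The weakness is that the plan relies on one form alone.

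All sizes rest on assumed values of rho, of the engagement-severity correlation and of the entry cut in SD units. Severity is low.

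**What to change.** In the total-effect regression, add as a covariate the baseline value of the outcome analysed: SDQ total for the SDQ model, and the matching ERC subscale (Lability/Negativity or Emotion Regulation) for each ERC model. Add the same baseline to the TWEETS regression and the joint model so that the coefficients are comparable. State whether the baseline SDQ sentence for the random-effect models is meant to reach the mediation models.

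Report the raw change-score version beside the adjusted one as a sensitivity analysis, and describe engagement as a mediator only if the two agree.

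The cost is a short change to the analysis text, one degree of freedom per model and one extra set of exploratory results. No new data are needed.
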